### Quality control, data management and monitoring

We designed an electronic data capture (EDC) system and an electronic case report form (eCRF) to capture and check all data. Patient information is collected and then entered into the CHANGE platform which was built on a secure Website (https://edc.einmatrix.com/studies). The investigators who enter information into the EDC system are responsible for ensuring accuracy and completeness of information. All electronic data are protected by encryption. Data management and monitoring are carried out by a dedicated project and data management team according to predefined procedures to avoid bias. Once abnormal or missing values are detected, queries will be sent by the EDC system automatically to local investigators to check and revise the data. To guarantee the data quality and follow-up rate, trained clinical research coordinators from the project and data management team will visit the participating centers if they have a large proportion of missing value or a lower follow-up rate to check the consistency between registered information and original medical records in randomly selected patients.

### Statistical analysis plan

Categorical variables will be presented as numbers and percentages. Normally distributed continuous variables will be shown as means ± standard deviations(SD), while non-normally distributed continuous variables will be presented as medians together with 25% and 75% percentiles. Multivariable logistic regression models will be used to determine independent factors and their magnitudes of associations with clinical outcomes during hospitalization. Time-to-event outcomes will be presented using Kaplan-Meier methods and hazard ratios and corresponding 95% confidence intervals (CI) will be derived from the Cox proportional hazards regression models. In addition, enrolled patients will be stratified into subgroups according to different study stages, age of patients, or therapeutic options etc. for further analyses. Statistical significance will be established at 2-tailed *P* value < 0.05. All statistical analyses will be performed in SAS 9.4 (SAS Institute Inc. Cary, NC, USA).

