Great progress has been made these years in the therapeutic strategy of CTEPH. CTEPH is potentially curable by pulmonary endarterectomy (PEA) in patients with surgically accessible thrombi in the main, lobar or segmental pulmonary arteries [5]. However, PEA is not feasible in all patients; up to a half of the patients are considered inoperable and up to 51% develop persistent/recurrent PH after undergoing PEA [6–9]. Balloon pulmonary angioplasty (BPA) is an option for CTEPH patients with lesions in the distal pulmonary arteries. The specific medication for pulmonary arterial hypertension (PAH) can also be used in patients with CTEPH, since they have similar pulmonary vessel remodeling. Due to the progress in the surgical and interventional therapy technic as well as the development of PAH specific therapy, the prognosis and life quality of patients with CTEPH have been improved. There is still a gap between the normalized management and real-world clinical practice. Moreover, qualified CTEPH centers, in which PEA and BPA can be performed with satisfactory quantity and quality, are quite limited in China. The existing studies on CTEPH have the limitations with long time-span and relative small sample size, in which limited patients received BPA or novel target therapy. Thus, they could not accurately reflect the current status in the new era of multimodality therapy in CTEPH.

In a large international CTEPH registry with 679 patients, the 3-year survival was 89% in operated patients and 70% in non-operated patients, respectively [10]. The 5-year and 10-year survival was 82 and 75%, respectively, reported by the University of California, San Diego in the United States, known as the most experienced center in PEA [11]. The therapeutic effect and long-term outcome of patients with CTEPH need to be identified in a large cohort in Asia. High-quality studies in the real world are required to further increase the understanding of CTEPH, including the clinical characteristics, management pattern, outcomes of CTEPH and related risk factors.

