### Follow-up and endpoints

The patients receive regular follow-up every 3 or 6 months after enrollment for at least three years. For each follow-up, they receive inquiry, physical examination, 6-minute walking test (6MWT), blood tests, electrocardiogram, ultrasonic cardiogram, VQ scan or CTPA and RHC. Cardiopulmonary exercise testing (CPET) and cardiac MR are arranged in selected patients. The therapeutic strategy is modified according to the assessment of each follow-up. If the patients are admitted to the hospital unexpectedly, the cause of hospitalization, the change of symptoms and treatment since last visit, 6MWD, WHO-FC and the change of PVR will be recorded.

The primary outcomes include all-cause mortality and changes in functional and hemodynamic parameters from baseline. The secondary outcomes include the proportion of patients experiencing lung transplantation, the proportion of patients experiencing heart and lung transplantation, and changes in health-related quality of life. The study outcomes were listed in Table 1.

**Table 1 Tab1:** Primary, secondary, and safety outcomes

Outcomes	Main indicators

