**Secondary outcomes**	
lung or heart and lung transplantation	proportion of patients experiencing lung or heart and lung transplantation due to severe right heart failure during the study
changes of health related quality of life	change of quality of life measured with the EQ-5D-5L or EmPHasis-10

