**Safety outcomes**	
bleeding	fatal bleeding, major bleeding, clinically relevant non-major bleeding, based on the ISTH definition [15, 16]
symptomatic recurrence of DVT or PE	reappearance of clinical manifestations or symptoms associated with DVT or PE after a previous episode or treatment, include leg pain, swelling, warmth, redness, or shortness of breath, etc.
complication of treatment interventions (PEA or BPA)	complications include lung injury, haemoptysis, residual pulmonary hypertension, etc.

6MWD: 6-minute walk distance; WHO-FC: WHO-functional class; BNP: brain natriuretic peptide; NT-proBNP: N terminal-probrain natriuretic peptide; mPAP: mean pulmonary arterial pressure; PVR: pulmonary vascular resistance; CO: cardiac output; CI: cardiac index; EQ-5D-5L: 5-level EQ-5D version; ISTH: international society on thrombosis and haemostasis; DVT: deep venous thrombosis; PE: pulmonary embolism; PEA: pulmonary endarterectomy; BPA: balloon pulmonary angioplasty

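### Kaplan-Meier is the only time-to-event estimator named and would overstate absolute risk if used for non-fatal outcomes; separately, the transplant proportion has no time horizon

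*Protocol article*

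**What the plan says.** The Statistical analysis plan section of the protocol article has one sentence on event-time data: "Time-to-event outcomes will be presented using Kaplan-Meier methods and hazard ratios". Cox models are to supply those ratios. The sentence does not list the outcomes to which it applies. The article nowhere mentions competing risks, cumulative incidence, or how a death is handled when another event is analysed. The same section plans subgroup analyses by study stage and by therapeutic option, among others.

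The outcomes that occur on a date are:
- All-cause mortality, which is primary: "The primary outcomes include all-cause mortality and changes in functional and hemodynamic parameters from baseline" (Follow-up and endpoints).
- Transplantation, which is secondary and defined in Table 1 as "proportion of patients experiencing lung or heart and lung transplantation due to severe right heart failure during the study".
- Safety outcomes in Table 1, including "fatal bleeding, major bleeding, clinically relevant non-major bleeding, based on the ISTH definition" and "symptomatic recurrence of DVT or PE". No estimator is attached to these.

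On mortality, the Introduction cites a large international registry in which "the 3-year survival was 89% in operated patients and 70% in non-operated patients, respectively". On timing, the Discussion places the launch in 2016, reports 1500 patients by 31 December 2023 and says that recruitment continues. Planned follow-up is at least 3 years per patient.

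**The concern.** A patient who dies can no longer be transplanted, bleed or have a recurrent embolism. Kaplan-Meier with deaths censored treats that patient as still at risk and assigns the future event rate of the survivors. The complement of the curve then estimates risk in a population in which nobody dies, which exceeds the proportion of patients who actually have the event. The excess grows with mortality, so it would be largest in the patients managed without surgery, and the plan proposes to stratify by therapeutic option.

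The transplant outcome has a different weakness. A proportion counted over the whole study rises with time under observation. Patients enrolled early have years more observation than those enrolled late, so a comparison of study stages would show a difference even if the transplant rate had never changed.

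**Working it through.** The article gives no non-fatal event rate and no competing-risk figure, so there is nothing of its own to reproduce.

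**Inputs**
- 3-year survival S: 0.89 operated, 0.70 non-operated (cited registry, Introduction; not a design assumption of this study).
- Event hazard h: assumed, varied below.
- Constant and independent hazards for event and death: assumed.

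**Part 1: Kaplan-Meier for a non-fatal event**

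Death hazard d = −ln(S)/3:
- Operated: −ln(0.89)/3 = 0.0388 per year.
- Non-operated: −ln(0.70)/3 = 0.1189 per year.

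One minus Kaplan-Meier at 3 years = 1 − exp(−3h).
Cumulative incidence at 3 years = h/(h+d) × [1 − exp(−3(h+d))].

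With h = 0.05 per year:
- One minus Kaplan-Meier: 1 − exp(−0.15) = 13.9% in both groups.
- Cumulative incidence, operated: 0.05/0.0888 × [1 − exp(−0.2665)] = 13.2%. The excess is 0.8 points, or 5.8% relative.
- Cumulative incidence, non-operated: 0.05/0.1689 × [1 − exp(−0.5067)] = 11.8%. The excess is 2.2 points, or 18.4% relative.

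Sensitivity to the assumed event rate, indexed by the 3-year value of one minus Kaplan-Meier:

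| 1 − KM | Operated: cumulative incidence (excess) | Non-operated: cumulative incidence (excess) |
|---|---|---|
| 2% | 1.89% (0.1 points, 5.9%) | 1.68% (0.3 points, 18.8%) |
| 10% | 9.45% (0.6 points, 5.8%) | 8.44% (1.6 points, 18.5%) |
| 30% | 28.42% (1.6 points, 5.6%) | 25.50% (4.5 points, 17.6%) |

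The relative excess hardly depends on the event rate. It is set by mortality and is about three times as large in the non-operated group. The absolute excess scales with the event rate.

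**Part 2: does a crude proportion share this error?**

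No. A crude proportion counts only events that happened before death. With complete 3-year follow-up and a one-minus-Kaplan-Meier value of 10%, a simulation of 2,000,000 patients per group gave 9.42% operated and 8.45% non-operated, against cumulative incidences of 9.45% and 8.44%. With an assumed 10% per year loss to follow-up the crude proportion falls below the true value: 8.15% against 9.45% operated, and 7.32% against 8.44% non-operated.

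**Part 3: crude proportion and length of follow-up**

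At December 2024 a patient enrolled at the end of 2023 has about 1 year of possible follow-up, and one enrolled at the end of 2016 about 8. Assume a constant transplant hazard of 1% per year and the death hazards above, with the cumulative incidence formula taken at time t:

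| Follow-up t | Operated | Non-operated |
|---|---|---|
| 1 year | 1.0% | 0.9% |
| 3 years | 2.8% | 2.5% |
| 8 years | 6.6% | 5.0% |

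Between 1 and 8 years the proportion differs five- to seven-fold with no change in the hazard. If every patient is first allowed to reach 3 years, the contrast between 3 and 8 years is still about two-fold (5.0/2.5 = 2.0 and 6.6/2.8 = 2.4).

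**The case against.** The strongest reply is that the article never says non-fatal outcomes will be shown by Kaplan-Meier. The sentence speaks of time-to-event outcomes in general, and the only outcome that is plainly of that kind is all-cause mortality, for which the method is correct. Transplantation is given as a proportion, and the safety outcomes have no estimator. A condensed article may also leave competing-risk methods to a full analysis plan that is not shown. This stands as far as the first part is conditional: the error arises only if the general rule is applied to non-fatal outcomes. It does not remove the point, because the rule is written without restriction and names no alternative.

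A reader might go further in four ways that the documents do not support:
- That the crude transplant proportion also overstates risk. It does not (Part 2 of the working). Its fault is the missing time horizon.
- That treatment comparisons by Cox model are distorted. A Cox model that censors deaths estimates the cause-specific hazard ratio, which is valid for association. In the example the two event hazards are equal and that ratio is correctly 1. Only absolute risks are wrong.
- That every safety outcome is affected. Fatal bleeding is itself a death, and complications of PEA or BPA arise largely around the procedure in treated patients only. A 3-year competing-death model does not describe either.
- That the changes from baseline must be ranked with death as the worst result. That is a preference, and nothing in the article is wrong for lacking it.

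It is also fair to say that the 89% and 70% come from another registry and that the Introduction describes prognosis as having improved, so 18% may be high for this cohort. The 1-year figure in Part 3 is a snapshot during recruitment, since the design intends at least 3 years for each patient. The two-fold contrast between 3 and 8 years answers that only in part, because it supposes that early patients continue to be followed beyond 3 years.

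**Conclusion.** The point holds in two separate and limited parts.

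First, if Kaplan-Meier is used for transplantation, non-fatal bleeding or symptomatic DVT/PE recurrence, the reported absolute risk is too high by about 6% relative in operated and 18% relative in non-operated patients. This rests on the cited survival, assumed event rates, and constant independent hazards. For a rare event the absolute error is minor: about 0.3 points for a 2% event in non-operated patients. Mortality analyses and cause-specific hazard ratios are sound as planned.

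Second, the transplant proportion is tied to no time point although enrolment spans 2016 to beyond 2023. This part does not depend on how the Kaplan-Meier sentence is read. Any comparison by study stage would confound risk with length of observation.

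Neither part touches the primary mortality result. Both affect descriptive figures that a registry of this kind exists to publish, and both are cheap to put right.

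**What to change.** - State which outcomes are analysed as time-to-event.
- Keep Kaplan-Meier for all-cause mortality, and for transplant-free survival if that is wanted.
- For transplantation, non-fatal bleeding and symptomatic DVT/PE recurrence, report Aalen-Johansen cumulative incidence at fixed times, for example 1 and 3 years, with death as the competing event. Give cause-specific hazard ratios beside it. Both are needed: with equal event hazards the non-operated group still has the lower cumulative incidence (11.8% against 13.2% in the example), only because more of its patients die first.
- Replace the transplant proportion over the whole study with the fixed-time cumulative incidence, and use that estimate for comparisons by study stage and therapeutic option.

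The cost is revised wording and slightly more analysis work in SAS 9.4, which the article already names. No new data are needed, provided that event dates are recorded, as any time-to-event analysis requires.

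### If bleeding and recurrent DVT/PE are shown by Kaplan-Meier, as the unqualified rule for time-to-event outcomes implies, their absolute risks will be overstated because death is a competing event

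*Protocol article*

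**What the plan says.** The Statistical analysis plan section of the protocol article gives one rule for follow-up events: "Time-to-event outcomes will be presented using Kaplan-Meier methods". It attaches no exception, does not list the outcomes covered, and pairs the curves with regression estimates from Cox models. Logistic regression, the only other event model named, is confined to "associations with clinical outcomes during hospitalization". The article nowhere mentions cumulative incidence or death as a competing event.

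Table 1 lists two safety outcomes that can arise at any time in follow-up: bleeding, defined as "fatal bleeding, major bleeding, clinically relevant non-major bleeding, based on the ISTH definition", and "symptomatic recurrence of DVT or PE". It gives no summary measure for either. Follow-up lasts at least three years (Follow-up and endpoints), and subgroup analyses by therapeutic option are planned. All-cause mortality is a primary outcome. The Introduction cites an earlier 679-patient international registry in which "the 3-year survival was 89% in operated patients and 70% in non-operated patients".

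**The concern.** Kaplan-Meier treats a censored patient as still able to have the event later. For all-cause mortality that causes no difficulty. For a bleed or a recurrent clot, a patient who has died can no longer have the event. Censoring at death therefore estimates the risk in a hypothetical population in which nobody dies of anything else. As an estimate of the proportion of patients who actually bleed or clot, 1 minus Kaplan-Meier is too high whenever some deaths come first.

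The Discussion makes the safety of anticoagulants under lifelong treatment an explicit interest of the registry, and absolute risks of bleeding and recurrence are what it would supply on that question. The planned subgroups by therapeutic option would also set side by side patients whose mortality, on the cited figures, differs nearly threefold. The relative overstatement would then differ between the curves shown.

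**Working it through.** The article states no bleeding rate, recurrence rate or event count, so there is no figure of its own to reproduce. The check asks how large the overstatement could be.

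**Inputs**
- 3-year survival S: 0.89 operated, 0.70 non-operated (Introduction, from the earlier registry).
- Horizon T = 3 years, the stated minimum follow-up.
- Event risk: assumed. The cases are a 3-year Kaplan-Meier risk of 5%, of 10%, and 5 events per 100 patient-years, each taken as equal in the two groups.
- Constant, independent hazards: assumed. All deaths are treated as competing.

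**Formulas**
- Death hazard: d = −ln(S)/3.
- Event hazard: e = −ln(1 − p)/3 for a 3-year Kaplan-Meier risk p, or the assumed rate itself.
- With deaths censored: 1 − KM = 1 − exp(−3e).
- Cumulative incidence: CIF = e/(e + d) × [1 − exp(−3(e + d))].

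**Death hazards**
- Operated: −ln(0.89)/3 = 0.0388 per year.
- Non-operated: −ln(0.70)/3 = 0.1189 per year, about three times as high.

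**Worked case, e = 0.05 per year**
- 1 − KM = 1 − exp(−0.15) = 13.93% in both groups.
- Operated: CIF = 0.5628 × 0.2340 = 13.17%. Overstatement 0.76 points; 13.93/13.17 − 1 = 5.8%.
- Non-operated: CIF = 0.2960 × 0.3975 = 11.77%. Overstatement 2.16 points; 13.93/11.77 − 1 = 18.4%.

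(Subtracting percentages already rounded to one decimal gives 0.7 and 2.1 points.)

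**Results at 3 years**

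| Assumed 1 − KM | Group | CIF | Excess (points) | Relative excess |
|---|---|---|---|---|
| 5% | operated | 4.72% | 0.28 | 5.9% |
| 5% | non-operated | 4.21% | 0.79 | 18.7% |
| 10% | operated | 9.45% | 0.55 | 5.8% |
| 10% | non-operated | 8.44% | 1.56 | 18.5% |
| 13.93% | operated | 13.17% | 0.76 | 5.8% |
| 13.93% | non-operated | 11.77% | 2.16 | 18.4% |

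The relative excess hardly depends on the assumed event rate. Over assumed Kaplan-Meier risks from 3% to 30% it stays at 5.6% to 5.9% (operated) and 17.6% to 18.8% (non-operated). A simulation of 1,000,000 patients per group at the 10% case gave cumulative incidences of 9.50% and 8.40% against 1 − KM of 10.06% and 9.96%, in line with the formulas.

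**Sensitivity**
- Timing of deaths, 10% case: if every death came before any event, the true incidence would be 0.10 × 0.89 = 8.9% and 0.10 × 0.70 = 7.0%. If every death came at 3 years, it would be 10% in both groups and there would be no overstatement.
- Lower mortality: if 3-year mortality were half the cited figures (5.5% and 15%), the relative excess in the 10% case would fall to 2.8% and 8.2%.
- Fatal bleeds are events, not competing deaths. Treating all deaths as competing therefore slightly overstates the excess for bleeding.

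**The case against.** The strongest reply is that the article does not commit itself to this error. It never calls bleeding or recurrence a time-to-event outcome. It also says "Categorical variables will be presented as numbers and percentages", which could cover both, and Table 1 defines the other non-fatal event, transplantation, as the "proportion of patients experiencing lung or heart and lung transplantation due to severe right heart failure during the study". Counts and percentages would not carry this bias, and a full analysis plan, not shown, may assign estimators outcome by outcome. This stands, and it makes the point conditional. It does not remove it: the time-to-event rule is stated without exception, logistic regression is limited to the hospital stay, and Kaplan-Meier with Cox is the only method named for events in follow-up. Crude percentages would not deal with unequal follow-up either.

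A second reply concerns size. The survival figures are not this cohort's. They come from a registry whose enrolment Table 2 dates to 2007–2009, and the article says that prognosis has since improved. The event rates are assumed. This also stands. At a 5% risk the error is under one percentage point in both groups.

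A reader might go further in three ways that the documents do not support:
- **That comparisons by therapeutic option are invalid.** Cox models with deaths censored estimate cause-specific hazard ratios, and these remain valid. In the worked case the event hazards are equal, and the gap between 13.17% and 11.77% arises from mortality alone. Which contrast is wanted depends on the question asked.
- **That the error is always largest where mortality is highest.** This holds in relative terms when events and deaths have similar timing. In absolute points it can reverse: operated patients at a 30% Kaplan-Meier risk have an excess of 1.58 points, non-operated patients at 10% have 1.56.
- **That much larger errors follow at later years.** Such figures would extend 3-year hazards beyond any non-operated survival that the article reports.

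**Conclusion.** The concern holds as a conditional point about absolute risks. Read plainly, the rule would put bleeding and DVT/PE recurrence on Kaplan-Meier curves, and those curves would read too high. The direction is certain if any deaths precede the event. The size rests on three assumptions: constant hazards, mortality like that of the cited earlier registry, and an event rate that the article does not give. On these, the overstatement at 3 years is about 6% relative in operated and about 18% in non-operated patients, or roughly 0.3 to 0.8 and 0.8 to 2.2 percentage points for Kaplan-Meier risks of 5% to 14%. Lower current mortality or later deaths would shrink it. The primary mortality analysis and the Cox hazard ratios are not in question. The change is worth making because it is cheap and concerns published safety risks, but it does not threaten the study's main result.

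**What to change.** - Limit the Kaplan-Meier sentence to all-cause mortality.
- Show bleeding and symptomatic DVT/PE recurrence by the Aalen-Johansen cumulative incidence function, with death from other causes as the competing event, overall and by therapeutic option. Count fatal bleeding as a bleeding event.
- Label the Cox hazard ratios for these outcomes cause-specific. A Fine-Gray model can be added if a contrast of cumulative incidence is wanted, but it is not needed.
- If the full analysis plan already assigns these outcomes to another summary, say so in place of the unqualified rule.

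The cost is about one sentence of text and one more procedure option in SAS 9.4, which the article already names (EVENTCODE= in PROC LIFETEST; PROC PHREG for the hazard ratios). No new data are needed beyond dates and causes of death. Reported risks will be slightly lower than Kaplan-Meier would give.

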### Therapeutic strategy

All the patients received a life-long anticoagulation, with warfarin, direct oral anticoagulants （DOACs） or low-molecular-weight heparin. The therapeutic strategy is made by a multidisciplinary team (MDT) consist of PH specialist, PEA surgeon, interventionist, radiologist experienced in thoracic imaging, anesthesiologist and intensive care specialist. The patients with surgically accessible thrombi in the main, lobar or segmental pulmonary arteries and who are willing to receive surgery will receive PEA. The patients who are considered inoperable in the first center will go for consultation in another PH center. BPA and PAH target medication are used in patients who are inoperable or unwilling to receive surgery, and who have recurrent PH after PEA, based on the experience of pulmonologist, cardiologist, and interventional radiologist in each center. Diuretics and cardiotonics are selectively used in the patients with right heart dysfunction. Patients whose cardiopulmonary function is stable also receive rehabilitation during hospitalization and at home.

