The multimodality treatment has been applied more widely in patients with CTEPH in recent years. Numerous unanswered questions and challenges continue to arise in the new era of multimodal CTEPH treatment. There are several scenarios of the multimodality therapy for CTEPH: (1) some patients with inoperable CTEPH receive sequential or simultaneous treatment with targeted medical therapy and BPA; (2) BPA and/or targeted medical therapy have been applied in patients with persistent or recurrent PH after PEA; (3) patients with operable CTEPH but severe hemodynamic impairment could receive PEA after several sessions of BPA ± targeted medical therapy with reduced surgical risk; (4) combination of PEA and BPA might be performed in selected patients with high-risk hemodynamics with unilateral operable and contralateral inoperable disease. It remains unclear which is the best sequence and interval of the hybrid of therapeutic strategy for selected patients. We will try to find the answer to these questions in the real-world study.

In the CHANGE registry, we will also focus on the medical treatment in patients with CTEPH in recent years, especially PAH-specific drugs and anticoagulants. Up to now, riociguat was the only agent approved for the treatment of CTEPH and used as first choice for all CTEPH patients who need PAH-specific therapy. However, riociguat was not available or not included in health insurance in some areas, that limit its application in clinical practice. In addition, other PAH-specific drugs, such as macitentan and subcutaneous treprostinil, also exhibited promising efficacy in CTEPH. PAH-specific drugs which appeared on the market earlier, like sildenafil, tadalafil, bosentan and ambrisentan, were chosen to treat patients with CTEPH when riociguat was not available or well tolerated. It remains to be illustrated which kind of PAH-specific agent and whether combined PAH-specific therapy bring benefit for patients with CTEPH. All the guidelines on CTEPH recommend life-long anticoagulation for CTEPH patients without contradiction. Nonetheless, the effect and safety of DOACs in CTEPH is still controversial and need to be illustrated in both randomized controlled trials and real-world studies.

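### Therapeutic option is listed as a fixed subgroup beside age with neither the option nor time zero defined; any grouping by treatment received after enrolment would carry immortal-time bias

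*Protocol article*

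**What the plan says.** The Statistical analysis plan section of the article gives the survival methods in one sentence: "Time-to-event outcomes will be presented using Kaplan-Meier methods and hazard ratios and corresponding 95% confidence intervals (CI) will be derived from the Cox" proportional hazards model. The next sentence adds that "enrolled patients will be stratified into subgroups according to different study stages, age of patients, or therapeutic options etc. for further analyses". A two-sided 5% significance level applies. The section does not say whether the option is the one assigned by the multidisciplinary team (MDT), the first one given or everything received. It names no time origin for survival and no time-dependent or landmark handling.

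Other sections show how treatment unfolds:

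- **Study objective and design; Follow-up and endpoints:** patients are newly diagnosed and are followed from enrolment for at least three years.
- **Baseline assessment:** initial therapy is recorded with the baseline data.
- **Therapeutic strategy:** the MDT sets the strategy, and patients judged inoperable are referred to another centre for a second opinion.
- **Follow-up and endpoints:** "The therapeutic strategy is modified according to the assessment of each follow-up".
- **Discussion:** "patients with operable CTEPH but severe hemodynamic impairment could receive PEA after several sessions of BPA". BPA or drugs may also follow PEA. The authors write that "It remains unclear which is the best sequence and interval of the hybrid of therapeutic strategy for selected patients", and say that they will try to answer this with the registry.

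All-cause mortality is among the primary outcomes.

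**The concern.** Age and study stage can serve as fixed strata because they are settled when follow-up begins. Treatment in this cohort is settled only as follow-up proceeds. To be counted as a PEA, BPA or sequential-treatment patient, someone must first survive to the procedure. If that later information defines a fixed group and the survival clock starts at enrolment, the waiting time is event-free by construction and is credited to the treated group. Patients who die while waiting count as untreated.

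The sequence and interval question makes this more than a wording matter. A sequence such as BPA followed by PEA is complete only in patients who lived through it, so no group known at enrolment corresponds to it. Answered with ordinary Kaplan-Meier curves and a Cox model with fixed groups, longer sequences would tend to look better even if they did nothing. A reader could take that for evidence on how treatments should be combined.

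**Working it through.** The article gives no hazard ratio, power calculation or waiting time for this study, so there is no figure to reproduce. The check asks how large a benefit appears when there is none.

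**Inputs**

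- From the Introduction: 3-year survival in an earlier international registry of 70% (non-operated) and 89% (operated). I use 70%, 80% and 89%.
- From Follow-up and endpoints: a 3-year horizon.
- Assumed: 50% or 60% of patients are destined for a procedure; exponential survival and exponential waits; median wait 1 to 12 months; no treatment effect.

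**Formulas.** Let S be 3-year survival, q the share destined for a procedure, death rate λ = −ln(S)/3, procedure rate μ = ln 2 / median wait in years, and k = μ + λ.

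- Fraction of destined patients who reach the procedure: p = (μ/k)(1 − e^(−3k))
- Fraction who reach it and are alive at 3 years: s = S(1 − e^(−3μ))
- Deaths after the procedure: q(p − s)
- Waiting time of those later treated: qμ[1 − e^(−3k)(1 + 3k)]/k²

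**Worked case.** Per 1,000 patients, S = 0.70, q = 0.60, median wait 6 months: λ = 0.1189, μ = 1.3863, k = 1.5052.

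- p = 0.9109, so 600 × 0.9109 = 546.6 patients are treated; s = 0.70 × 0.9844 = 0.6891.
- Deaths: treated 600 × (0.9109 − 0.6891) = 133.1; untreated 300 − 133.1 = 166.9.
- Person-years: total 300/0.1189 = 2,523.3; after the procedure 133.1/0.1189 = 1,119.7; waiting time of the treated 345.0.
- Grouped by treatment received, clock from enrolment: treated 133.1/(1,119.7 + 345.0) = 0.0909; untreated 166.9/(2,523.3 − 1,464.7) = 0.1576. **Rate ratio 0.58.**
- Apparent 3-year survival: treated 0.6891/0.9109 = 75.6%; untreated (700 − 413.4)/453.4 = 63.2%. The truth is 70% in both.
- Waiting time moved to the untreated side: 133.1/1,119.7 = 0.1189 and 166.9/1,403.6 = 0.1189. **Rate ratio 1.00.**

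**Range, true ratio 1** (each range spans 3-year survival of 70% to 89%)

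| Median wait | 50% destined | 60% destined |
|---|---|---|
| 1 month | 0.911–0.919 | 0.892–0.901 |
| 2 months | 0.835–0.846 | 0.802–0.815 |
| 4 months | 0.711–0.722 | 0.664–0.675 |
| 6 months | 0.626–0.633 | 0.577–0.583 |
| 12 months | 0.523–0.524 | 0.483–0.484 |

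The survival assumption hardly matters; the wait and the treated share do.

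**Cox models.** Simulated trials of 1,500 patients (the enrolment reported in the article), 50% destined, 200 replicates per scenario, waits given as means. The last column is how often a significant false benefit appeared, against a nominal 2.5%.

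| Mean wait | Spurious hazard ratio | False benefit |
|---|---|---|
| 1 month | 0.93 | 6.5%–12.5% |
| 3 months | 0.83–0.84 | 20.5%–51.5% |
| 6 months | 0.70–0.71 | 56.5%–97% |
| 12 months | 0.56–0.57 | 91.5%–100% |

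Over these scenarios and three more with 80% destined, treatment as a time-dependent covariate gave hazard ratios of 0.98 to 1.01, and grouping by the strategy assigned at enrolment gave 0.99 to 1.02.

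**The case against.** The strongest reply is that the article does not commit the error. It says therapeutic options and never says treatment received. Initial therapy is recorded at baseline and the MDT sets a strategy, so an unbiased first-strategy grouping is available. The subgroup sentence follows the survival sentence without naming a method or a contrast. The article is also a condensed account, and a full plan may define the exposure properly.

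Much of this stands. A reader might infer that the plan groups patients by what they eventually received; the text does not say so. A reader might also infer that the primary mortality result is biased. It is not: survival of the whole cohort does not depend on how treatment groups are formed. Nor does the article promise an answer on sequence; the Discussion says only that the authors will try.

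It is also tempting to add that the Cox model ignores centre. The section lists no Cox covariates at all, so that would be an argument from silence. The phrase "based on the experience of pulmonologist, cardiologist, and interventional radiologist in each center" concerns BPA and targeted drugs, not PEA.

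What the reply does not reach is the sequence and interval question. A first-strategy grouping cannot answer it, and the methods named have no unbiased fixed grouping for it. The objection is to a stratum that the article does state, in a section that sets methods, strata and significance level, and not to missing detail.

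**Conclusion.** The point holds in a conditional form. The article lists therapeutic option as a stratum of the same kind as age, without defining it or time zero, in a cohort whose treatment starts and changes after enrolment. Any fixed grouping by treatment received would carry immortal-time bias, and the stated interest in sequence and interval would need such a grouping under the named methods.

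With no true effect, the spurious hazard ratio is about 0.9 at a 1-month median wait and about 0.5 at 12 months. This rests on an assumed 50% to 60% destined for a procedure and on assumed exponential waits; the documents give neither the share nor the waits. With prompt treatment the bias is small. Whole-cohort mortality and comparisons by a strategy fixed at enrolment are not affected. Confounding by operability and disease severity is a separate problem, which correct handling of time does not remove.

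**What to change.** Amend the Statistical analysis plan section to state that:

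1. Time zero is enrolment (diagnosis) for every survival analysis.
2. Fixed strata are limited to features known at time zero: age, study stage, and the MDT-assigned or initial strategy. Initial strategy must mean the one decided at time zero; if it means the first procedure actually delivered later, the bias returns.
3. PEA, first BPA and each drug class enter the Cox model as time-dependent covariates that switch on at the procedure or start date, with adjustment for baseline severity and operability.
4. Survival curves by treatment received are drawn only from a prespecified landmark, among patients alive at that time and grouped by treatment received up to it.

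Clone-censor-weight analysis for the sequence question, baseline hazards stratified by centre and centre-robust standard errors are worthwhile options but not part of the required change.

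The cost is wording and programming, provided procedure and drug start dates are held. The article shows that treatment and its changes are recorded but does not say that exact dates are, so this should be confirmed. The small statistical price is wider intervals and the loss of pre-landmark deaths from the landmark curves.
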